## Abstract

**Background:**

In patients with severe calcific aortic stenosis, balloon aortic valvuloplasty (BAV) is routinely performed in order to pre-dilate the stenosed aortic valve prior to transcatheter aortic valve implantation (TAVI). Although pre-dilation is considered to be essential for the preparation of the valve landing zone, there is no clear evidence to support its clinical value. In contrast, BAV has been suggested to be linked to several complications. Notably, while preliminary evidence has supported the feasibility and safety of TAVI without pre-dilation, larger studies directly comparing the benefit/risk profile of TAVI in the presence and absence of pre-dilation are required.

**Methods/Design:**

Therefore, a prospective, two-armed, multicenter registry (EASE-IT) was designed to obtain essential data concerning procedural success rates, adverse events, and mortality in a large cohort of patients undergoing transapical (TA)-TAVI using the Edwards SAPIEN 3 balloon expandable heart valves with and without pre-ballooning.

**Discussion:**

Data provided by EASE-IT will be used to assess the relevance of BAV during the TAVI procedure and to investigate associations between patient characteristics and outcomes. Therefore, results obtained from the EASE-IT registry could contribute to reduced rates of TAVI-associated morbidity and mortality in patients with severe, calcific aortic stenosis.

**Trial registration:**

ClinicalTrials.gov Identifier: NCT02127580

## Background

Degenerative aortic stenosis (AS) is characterized by the narrowing of the aortic heart valve and most frequently is associated with progressive calcification and fibrosis of the valve leaflets. It represents the most common form of valve disease in the Western world and is associated with an estimated 5-year survival rate of 32% in the absence of treatment [1–3]. Thus, severe symptomatic AS constitutes a class I indication for aortic valve replacement surgery [4]. In this regard, conventional surgery has proven to be safe and effective for eligible patients [5, 6]. However, open heart surgery cannot be performed in 30–40% of patients due to advanced age and/or comorbidities [1, 7]. For this reason, transcatheter aortic valve implantation (TAVI), which was first described by Cribier et al. [8, 9], has emerged as a ground-breaking alternative technique for valve delivery in elderly, mostly fragile patients. Indeed, the TAVI approach has shown similar efficacy as compared to surgery and survival benefits in patients where surgery cannot be performed (PARTNER) [10–12]. Since its introduction into clinical use, continuous efforts have been undertaken to evaluate and improve TAVI techniques with the objective of reducing TAVI-associated complications.

Since the introduction of TAVI [8, 9], pre-dilation of the aortic valve has been considered as an obligatory step prior to transcatheter heart valve (THV) placement. BAV is carried out under rapid right ventricular pacing (>180 bpm) for up to 30 seconds in order to facilitate the crossing of the aortic annulus and to enable full balloon-inflation for 3–5 seconds with the associated obstruction of the aortic annulus. Potential advantages of performing BAV before replacement of the aortic valve may be the following: sizing evaluation when injecting above the inflated balloon, checking the risk for coronary occlusion and supporting evidence for coronary protection in selected cases, checking for pacemaker capture in real-time, checking for “balloon jump” in cases with LVOT obstruction or mitral prosthesis, and checking the synchronization of operating team [13]. Though, BAV has been suggested to be associated with the following serious complications [14–17]: (1) hemodynamic failure such as prolonged hypotension, need for cardiopulmonary reanimation, cardiac tamponade; (2) arrhythmia requiring medical treatment or AV block with need for pacing; (3) vascular events like systemic embolism or myocardial infarction; and (4) bleeding due to cardiac perforation, trauma-mediated aortic root rupture etc. Therefore, due to these potentially life-threatening complications, it has been suggested that removal of the pre-dilation step might reduce the rates of adverse events in patients undergoing TAVI [18–20].

So far, only preliminary studies have investigated the clinical value of pre-dilation of stenosed aortic valves in patients receiving self-expandable THVs through the transfemoral (TF) route [18, 19] or balloon expandable valves via the transapical (TA) route [20]. In a pilot study by Grube et al., the feasibility and safety of TF-TAVI in the absence of pre-dilation was studied using the self-expandable Medtronic CoreValve (MCV) device in 60 consecutive patients within 13 centers [18]. A technical success rate of 96.7% was observed, with post-dilation required in 16.7% of the cases and an in-hospital mortality rate of 6.7%. Thus, the procedure was reported to display a safety and efficacy profile that was similar to that of the standard approach with dilation. In addition, Mendiz et al. conducted a study of 51 patients undergoing TF-TAVI without pre-dilation using the MCV device within a single center, observing a procedural success rate of 94.2% and an in-hospital mortality rate of 3.9% [19]. However, only one pilot study involving six patients has examined TA delivery of balloon expandable Edwards SAPIEN THVs in the absence of BAV [20]. Successful deployment was observed in all patients and elimination of the pre-dilation step was suggested to result in shortened procedural duration, decreased radiation exposure, and reduced usage of contrast agents. It was also proposed that TA-TAVI without BAV might diminish the likelihood of hemodynamic instability in patients with impaired LVEF.

Although these preliminary investigations have started to evaluate the safety of TAVI without pre-dilation, larger datasets directly comparing TAVI in the presence and absence of BAV are required to fully assess the risks and/or benefits associated with elimination of the pre-dilation step. For this reason, we have designed a prospective, two-armed, multicenter registry (EASE-IT) to compare the safety and efficacy of TA-TAVI using Edwards SAPIEN 3 with and without pre-ballooning. EASE-IT aims to document adverse events, mortality, and procedural data in order to assess the importance of pre-dilation during TAVI and to identify potential associations between patient characteristics and outcomes.

### Methods/Design of EASE-IT

EASE-IT is a multicenter, prospective, two-armed, observational registry. Enrollment of 200 subjects will take place at up to 10 study-sites in Germany. Approval was obtained by the Ethics Committee of the Landesärztekammer Stuttgart on February 25^th^ 2014 and confirmation obtained at each site participating in ROUTE prior to patient enrollment. All patients are required to provide written informed consent prior to participation. The investigation commenced in April 2014.

### Site selection

Sites are selected based on prior experience with TA-TAVI (i.e., minimum of 20 prior implantations) and the ability to enroll a minimum of two patients per month. All participating sites have been, independent of this registry, trained in the use of the Edwards SAPIEN 3 and Ascendra Balloon Catheter according to the manufacturer’s instructions for use (Edwards Lifesciences, Irvine, CA, USA) and by means of exhaustive fundamentals training (i.e., didactic sessions, case observations, device preparation, and simulator training). This will be followed by on-site training as specified by the Edwards Standard Operating Procedure.

### Patient selection

Patient eligibility for EASE-IT will be based on the following criteria: (1) indication for TAVI in accordance with the Edwards SAPIEN 3 instructions; (2) eligibility for TAVI with and without BAV; and (3) at least 18 years of age. Patients with contraindications based on instructions for use of either TAVI or the Ascendra Balloon Catheter will be excluded from the study. Additionally, patients meeting any of the following criteria will be excluded: (1) logistic EuroSCORE I >50%; (2) mitral or tricuspid valvular insufficiency (> grade II); (3) previous aortic valve replacement; (4) uncontrolled atrial fibrillation; (5) left ventricular or atrial thrombus by echocardiography; (6) recent cerebrovascular event (within the last 3 months);and (7) high probability of non-adherence to follow-up requirements (due to social, psychological, or medical reasons). Each participating center must document 10 consecutive cases with BAV and 10 cases without BAV.

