### Procedure

Notably, TA-TAVI with pre-dilation is to be performed as previously described by Walther et al. [13], whereas the procedure without pre-dilation will be carried out in a similar manner to that described by Wendler et al. [20]. Pre-operation computed tomography will generally be used for valve sizing purposes. However, investigators can modify these procedures to fit their needs. Patients will be assigned into groups (i.e., with BAV or without BAV) by their physician prior to study enrollment and independent of the registry.

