### Statistics

The sample size for EASE-IT was established based on previously reported event rates and the feasibility to detect an absolute risk reduction for the primary endpoint of 13% at 30 days while taking into consideration a 10% drop out rate [18, 20]. Intention-to-treat analysis, based on all patients enrolled in the registry will be performed. Subjects are considered registry participants when they enter the cath lab/hybrid suite. Descriptive data summaries will be used to present and summarize the collected evaluation data. For categorical variables (e.g. gender) frequency distributions will be given. For numeric variables (e.g. patient age) minimum, maximum, mean, median and standard deviation will be calculated. Linearized rates and actuarial probability statistics may be used where appropriate for adverse event reporting. Kaplan-Meier analysis will be performed for survival outcomes and where appropriate for adverse event outcomes.

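### The centre sampling rule requires consecutive cases only in the BAV (control) arm, and the article does not say how a fixed 10 + 10 per centre fits with independently made treatment choices

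*Protocol article*

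**What the plan says.** The sampling rule is one sentence under Patient selection: "Each participating center must document 10 consecutive cases with BAV and 10 cases without BAV". The same section makes "eligibility for TAVI with and without BAV" an inclusion criterion, so for every enrolled patient the choice of technique is discretionary.

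Under Procedure, patients are allocated to a group "by their physician prior to study enrollment and independent of the registry". Under Pre-defined objectives, outcomes are compared between the two groups, with the pre-dilated group as control. Site selection asks for "the ability to enroll a minimum of two patients per month", and Methods/Design of EASE-IT states that "Enrollment of 200 subjects will take place at up to 10 study-sites in Germany".

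The limitations section accepts that leaving the choice to investigators in a non-randomised registry may bias the comparison, and offers suitability for either technique as partial mitigation. It does not mention the per-centre number, the placing of the word *consecutive*, or the periods over which the two series are collected. The article gives no order for the two series and does not say what happens once one of them is full.

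**The concern.** Two separate matters arise from the one sentence.

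The first is who gets documented. A consecutive series removes the centre's discretion over which treated patients enter the data. If that protection covers the control arm only, the comparator arm may be a selected series, and the difference between arms then mixes the effect of technique with the effect of selection. Suitability for either technique does not prevent this, because it limits who may be documented and not who is. Later analysis cannot recover patients who were never recorded.

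The second is how an equal number per centre is reached when the choice of technique is made outside the registry. A centre whose habit is uneven either lets the quota influence the choice or goes on collecting one series after the other has closed. In the latter case the later cases have no concurrent control from the same centre, and technique becomes partly mixed with calendar time and growing experience. An uneven habit is plausible: the Background describes pre-dilation as long regarded as a necessary step and reports a single six-patient pilot of transapical delivery without it.

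**Working it through.** **The plan's own figure.** 10 centres × (10 + 10) = 200, which matches the stated enrolment, or 100 per arm. The quota and the total agree, and nothing below changes either.

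**Inputs.** From the article: 10 cases per series per centre, and at least 2 patients per month per site. Assumed: 2 per month is the flow of eligible patients, and each patient receives BAV with probability *p*, independently of the registry. The article gives no value for *p*, so a range is shown.

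**Chance that the quota fits by itself.** The probability that 20 consecutive eligible patients split exactly 10/10 is C(20,10) × *p*^10 × (1 − *p*)^10. At *p* = 0.5 this is 184,756 × 0.5^20 = 0.176. Even a centre with no preference usually does not meet the quota with its first 20 patients.

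**Gap if choices stay independent and each series is simply filled.** The table gives means over 20,000 simulated centres per value of *p*. Months are cases divided by 2.

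| BAV share | P(exact 10/10) | Eligible cases until both full | Undocumented (minus 20) | Gap between closings, cases | Gap, months |
|---|---|---|---|---|---|
| 50% | 0.176 | 23.6 | 3.6 | 7.1 | 7.1/2 ≈ 4 |
| 60% | 0.117 | 25.9 | 5.9 | 10.1 | 10.1/2 ≈ 5 |
| 70% | 0.031 | 33.5 | 13.5 | 19.4 | 19.4/2 ≈ 10 |
| 80% | 0.002 | 50.0 | 30.0 | 37.5 | 37.5/2 ≈ 19 |

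**Hand checks.** The mean closing positions of the two series add to 10/*p* + 10/(1 − *p*), so gap = 2 × (mean cases until both full) − [10/*p* + 10/(1 − *p*)].
- At 80%: 2 × 50.0 − (12.5 + 50) = 37.5.
- At 70%: 2 × 33.5 − (14.29 + 33.33) = 19.4.
- Using average rates only, at 80% the BAV series fills in 10/(2 × 0.8) = 6.25 months and the other in 10/(2 × 0.2) = 25, a gap of 18.75.
- At 70% the same calculation gives 7.1 and 16.7 months, a gap of 9.5.

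**Price of dropping the fixed numbers.** If centres took all comers and the overall split became n1:n2, the standard error relative to 100:100 would be about √[(1/n1 + 1/n2)/(2/100)], treating the outcome variance as equal in the arms.
- 130:70 gives 1.048.
- 140:60 gives 1.091.
- 160:40, the 80% habit across all centres, gives √(0.03125/0.02) = 1.25.

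The confidence interval would thus be about 5%, 9% or 25% wider.

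**The case against.** A reader might infer that the quota contradicts independent assignment. It does not. The Procedure section governs who chooses the technique, and the sampling rule governs what a centre records. A registry can take a fixed number from each of two independently formed groups without changing anyone's treatment. What stands is that the article does not say this is how the rule works, and a centre can meet the quota in either way.

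A reader might also infer that calendar-time bias is part of the design. No order of the two series is stated, so it is a foreseeable risk and no more. The month figures depend on assumed habits and on treating a site's minimum enrolment capacity as its flow of eligible patients. A busier centre would have a proportionally shorter gap. No document gives an 80:20 habit, and in that case the centre would add only 2 × 0.2 = 0.4 documented patients per month once the BAV series had closed, well under the site criterion.

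It can further be said that *consecutive* was meant to carry over to both series. That is possible, but the sentence as printed does not say so. The direction of any bias is also unknown: it favours the no-BAV arm only if easier cases are documented there, and nothing in the article indicates that they are.

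Finally, the quota has a merit. Equal numbers within each centre keep technique from being confounded with centre, and the experience requirement (at least 20 prior transapical implantations, plus device training) limits the learning-curve argument without removing it. Both points stand and shape the remedy. The general disclosure of discretionary assignment also stands, but it does not cover selective documentation.

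**Conclusion.** The point holds in a limited form. As written, the rule protects only the control arm against selective documentation, in a registry whose main output is a direct comparison of the arms. That follows from the text and needs no assumption about centre habits. The size of any resulting bias cannot be calculated from the article.

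The quota is in tension with independent assignment and needs explaining. If choices remain independent, the two series close on average about 4 months apart at an even split, 10 at 70:30 and 19 at 80:20, and about 4, 14 and 30 eligible cases per centre go undocumented. These figures rest on the assumed splits and on 2 eligible patients per month. The documents do not support calling this a contradiction or a built-in time bias.

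**What to change.** Reword the sentence under Patient selection along these lines: *each centre documents consecutive eligible patients in both groups, 10 with BAV and 10 without BAV, with both series starting on the same date.* Surplus cases in the faster series then go undocumented by rule and not by choice.

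Keep the 10 + 10 per centre. Turning it into a target would give up within-centre balance and, with a strong habit across sites, could widen the confidence interval by up to the 25% shown above.

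Add a sentence that the quota must not influence the choice of technique.

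Wherever the adjusted or sensitivity comparison is specified, include procedure date or case number together with centre. This reduces the effect of unequal calendar windows but does not remove it, since late cases may have no concurrent control at their own centre.

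A short count per centre of eligible patients not documented would be useful but is optional.

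The cost is slightly less freedom for sites, possibly slower filling of one series, and a little more analysis work. The sample size is unchanged. The article says the registry started in April 2014, so the rewording can protect only cases not yet documented.

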### Procedure

Notably, TA-TAVI with pre-dilation is to be performed as previously described by Walther et al. [13], whereas the procedure without pre-dilation will be carried out in a similar manner to that described by Wendler et al. [20]. Pre-operation computed tomography will generally be used for valve sizing purposes. However, investigators can modify these procedures to fit their needs. Patients will be assigned into groups (i.e., with BAV or without BAV) by their physician prior to study enrollment and independent of the registry.

### Pre-defined objectives

The primary evaluation criteria at 1 month will consider the combined endpoint of all-cause mortality, stroke, non-fatal myocardial infarction, acute kidney injury, and pacemaker implantation within 30 days after TAVI as to VARC2 (Figure 1). Secondarily, the rates of each of these individual adverse events will be considered, along with duration of radiation, amount of contrast agent, and aortic root rupture. Six months after TAVI, the combined and separate adverse events will once again be evaluated. Patient outcomes will be compared between the two groups, with implantation plus pre-dilation considered as the control arm.

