**Table 1 Tab1:** **Data collection**

Parameter	Admission	Intervention	Discharge	30d FU	6 Mo FU
Inclusion/Exclusion criteria	X				
Demographics	X				
Diagnosis of valve disease	X				
Echocardiography	X				
Symptoms	X			X	X
Cardiac baseline characteristics	X				
ECG	X		X		
Comorbidities	X				
Risk scores	X				
Prior cardiovascular intervention	X				
Current medications	X		X	X	X
Interventional details		X			
Interventional results		X			
AE		X	X	X	X
Hospitalization duration			X		
Creatinine value	X		X		
Early safety/Clinical efficacy				X	X

A total of 20% of the sites (i.e., up to two sites) will be selected at random for monitoring following completion of patient follow-up and documentation. Source data verification will be performed for all patients in these centers. Also, 100% source data verification will be conducted for the following serious adverse events: death, stroke, major bleeding, valve complications, vascular complications, permanent pacemaker implantation, and renal failure. For data analysis, linearized rates and actuarial probability statistics will be used for adverse event reporting, and Kaplan-Meier analyses will be performed for survival and adverse event outcomes when appropriate.

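### Acute kidney injury counts in the 30-day and 6-month composites, but creatinine is scheduled only at admission and discharge, so other kidney injury rests on investigator reporting

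*Protocol article*

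**What the plan says.** Under Pre-defined objectives, the primary evaluation is a composite of "all-cause mortality, stroke, non-fatal myocardial infarction, acute kidney injury, and pacemaker implantation within 30 days after TAVI", with VARC2 definitions. AKI is thus one of five components, with a 30-day window and a cited definition. The same section adds: "Six months after TAVI, the combined and separate adverse events will once again be evaluated". AKI therefore counts at both horizons, within the composite and on its own.

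Table 1 (Data collection) has a row "Creatinine value", marked at Admission and Discharge. The Intervention, 30-day and 6-month columns are empty in that row.

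Two other rows can carry AKI. Adverse events are collected at Intervention, Discharge, 30 days and 6 months. The item "Early safety/Clinical efficacy" is collected at 30 days and 6 months. The text after Table 1 requires complete source data verification for a list of serious adverse events: "death, stroke, major bleeding, valve complications, vascular complications, permanent pacemaker implantation, and renal failure". The list includes renal failure and does not name AKI. All patients are verified only at the randomly chosen 20% of sites, at most two.

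**The concern.** A component of the primary endpoint should be found in the same way in every patient. Of the five components, AKI is the one that Table 1 supports with a scheduled laboratory value, and the two scheduled values do not span the window in which it counts. A rise after the procedure that has settled by discharge leaves the admission and discharge values looking alike. A rise that begins after discharge has no scheduled value at all. If the discharge entry is the last value of the stay, it also falls on a different post-procedural day in each patient.

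What remains is investigator reporting. The Procedure section has the treating physician choose the arm, so those who report are not blind to it. Clinically obvious AKI will probably be recorded. Mild or short-lived AKI depends on how closely each site looks and on what it regards as reportable.

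This bears on the registry's question. The Discussion lists renal ischaemia among the transient ischaemic effects linked to pre-dilation, and the Background cites a six-patient pilot that suggested "shortened procedural duration, decreased radiation exposure, and reduced usage of contrast agents" without it. A transient renal effect is the kind that a discharge value is least able to show. Equal under-detection in both arms shrinks the absolute difference; unequal under-detection can move it in either direction.

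**Working it through.** **Schedule against endpoint**

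| Period in which AKI can occur | Counts in composite? | Scheduled creatinine | Other route |
|---|---|---|---|
| After the procedure, still present at discharge | 30 days and 6 months | Admission and discharge pair | Adverse event report |
| After the procedure, resolved by discharge | 30 days and 6 months | Not visible in the pair, if the discharge entry is a last value | Adverse event report |
| Discharge to day 30 | 30 days and 6 months | None | Adverse event report; early safety item at 30 days |
| Day 30 to 6 months | 6 months | None | Adverse event report; same item at 6 months |

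Only the first row can be settled uniformly from scheduled values.

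**Stated figures.** The point contests no number in the article. The planned size is given as "Enrollment of 200 subjects will take place at up to 10 study-sites in Germany", with a 13-point reduction and 10% dropout (Statistics). The control rate, alpha, sidedness and power are not printed, so 200 cannot be rebuilt from the article alone. By assumption it fits, for example, a 17% control rate (two-sided 5%, 80% power: 87 per arm, 194 in total) or 21% (one-sided 5%, 80% power: 90 per arm, 200 in total).

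**Illustration of consequence.**

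From the article: 200 × (1 − 0.10) / 2 = 90 evaluable per arm, and a 13-point reduction.

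Assumed: composite rates pC and pT; a share f of events that are AKI only; a proportion s of those detected; a two-sided 5% test.

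Observed rate = p × (1 − f + f × s).

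Power = Φ{[√n × (pC − pT) − 1.96 × √(2p̄(1 − p̄))] / √(pC(1 − pC) + pT(1 − pT))}, with n = 90 per arm and p̄ the mean of the two observed rates.

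With pC = 0.25, pT = 0.12 and s = 0.5 in both arms:
- Full detection: 0.25 − 0.12 = 0.130; power 61%.
- f = 0.2: 0.25 × 0.9 = 0.225 and 0.12 × 0.9 = 0.108; difference 0.117; power 56%.
- f = 0.4: 0.25 × 0.8 = 0.200 and 0.12 × 0.8 = 0.096; difference 0.104; power 50%.

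With pC = 0.20 and pT = 0.07, the differences are the same and power falls from 73% to 67% (f = 0.2) or 62% (f = 0.4).

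**Unequal detection.** Keep 0.25 versus 0.12 and f = 0.4. If half of the AKI-only events are found without pre-dilation and all with it, the observed difference is 0.25 − 0.096 = 0.154. If the reverse holds, it is 0.200 − 0.12 = 0.080. The true difference is 0.13 in both cases. These are extremes, chosen to show direction.

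**The case against.** The strongest objection is that AKI outside the two values is not lost. Adverse events are collected at four visits, the early safety item at two, and the endpoint already has a cited definition in VARC2. Reported renal failure is fully verified against source. This stands. A reader might infer that transient and post-discharge AKI are simply missed, or that the 6-month count has no laboratory basis. The article does not support either. Recognised AKI has a reporting route throughout, and a report may rest on unscheduled laboratory results. What is absent is a scheduled value. Verification limits the gap without closing it: as described, it checks listed serious events and is not a search for unreported or milder AKI.

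A second objection is that Table 1 lists topics, not case report form fields. Its Discharge column also holds duration of hospitalisation, which describes the whole stay, so the creatinine entry there might be a peak value, or the adverse event form might ask for one. This stands as a possibility. Still, the article does print a creatinine row with fixed visits, and that stated schedule fits the endpoint poorly unless the row means more than it says.

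A third objection concerns size. One could assume true AKI of 15% versus 8%, with 30% to 60% of cases recovered by discharge. The visible difference then falls from 7 points to 10.5% − 5.6% = 4.9 points, or to 6.0% − 3.2% = 2.8 points. That describes the creatinine pair alone: it sets adverse event capture to zero and ignores patients already counted through another component. It is not an estimate of the loss in the composite. Nor does the article single out AKI as the main route of benefit; renal ischaemia is one item among several.

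**Conclusion.** The point holds in a limited form. The scheduled creatinine values cannot determine AKI uniformly over 30 days or 6 months. AKI that resolves before discharge or starts after it depends on reporting by investigators who know the arm. Mild, transient or later AKI may be under-ascertained, and possibly unevenly between sites or arms; the article does not show that it will be.

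The size cannot be derived from the document. Under the assumptions shown, with half of AKI-only events detected equally in both arms, the 13-point difference loses 1.3 to 2.6 points and power falls by about 5 to 11 percentage points. The composite rates, the AKI share and the detection proportion are all assumed. The conclusion also rests on the discharge entry being a single late value; if it is already the in-hospital peak, the gap is confined to the period after discharge. This is a worthwhile improvement to the measurement of a primary component, and it does not invalidate the design.

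**What to change.** 1. In Table 1 and the electronic case report form, add the highest post-procedural creatinine before discharge, with its date, abstracted from routine ward results that already exist. If the form already captures this, say so in Table 1.
2. Derive in-hospital AKI in both arms from the admission value and that peak, under the VARC2 definition already cited.
3. Keep AKI after discharge as reported adverse events. State that the post-discharge part of the 30-day and 6-month counts has no scheduled laboratory value behind it.
4. Do not limit the AKI component to the index stay unless the cited VARC2 definition requires it. The article does not print that definition's time window, so the sponsor should check it. A restriction without that basis would narrow the stated endpoint and discard later events that can now be reported.

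The cost is a little extra abstraction per patient. The change asks for no new test, but it depends on routine ward creatinine being available at each site, which the article does not document. Patients with no post-procedural value other than the discharge one should be identifiable in the data.
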